# Treatment duration of febrile urinary tract infection (FUTIRST trial): a randomized placebo-controlled multicenter trial comparing short (7 days) antibiotic treatment with conventional treatment (14 days)

**DOI:** 10.1186/1471-2334-9-131

**Published:** 2009-08-19

## Abstract

**Background:**

Current guidelines on the management of urinary tract infection recommend treating febrile urinary tract infection or acute pyelonephritis with antimicrobials for at least 14 days. Few randomized trials showed the effectiveness of treatment durations of 5 to 7 days but this has only been studied in young previously healthy women.

**Methods/Design:**

A randomized placebo-controlled double-blind multicenter non-inferiority trial in which 400 patients with community acquired febrile urinary tract infection will be randomly allocated to a short treatment arm (7 days of ciprofloxacin or 7 days of empirical β-lactams ± gentamicin intravenously with early switch to oral ciprofloxacin followed by 7 days of blinded placebo) or standard treatment arm (7 days of ciprofloxacin or 7 days of empirical β-lactams ± gentamicin intravenously with early switch to oral ciprofloxacin followed by 7 days of blinded ciprofloxacin). The study is performed in the Leiden region in which one university hospital, 6 general hospitals and 32 primary health care centers are clustered. Patients eligible for randomization are competent patients aged 18 years or above with a presumptive diagnosis of acute pyelonephritis as defined by the combination of fever, one or more symptoms of urinary tract infection and a positive urine nitrate test and/or the presence of leucocyturia. Exclusion criteria are known allergy to fluoroquinolones, female patients who are pregnant or lactating, polycystic kidney disease, permanent renal replacement therapy, kidney transplantation, isolation of ciprofloxacin-resistant causal uropathogen, renal abscess, underlying chronic bacterial prostatitis, metastatic infectious foci and inability to obtain follow-up. The primary endpoint is the clinical cure rate through the 10- to 18-day post-treatment visit. Secondary endpoints are the microbiological cure rate 10- to 18-day post-treatment, the 30- and 90-day overall mortality rate, the clinical cure rate 70- to 84-day post-treatment, relapse rate of UTI and adverse events or complications during 90 days of follow-up.

**Discussion:**

This study aims to demonstrate that 7 days of antimicrobial treatment is non-inferior as compared with 14 days of treatment in patients with febrile urinary tract infection. In addition, it will generate insights into the side-effects of antimicrobial treatment in relation to its duration. The study population will also include men, the elderly and patients with significant co-morbidity. Reflecting daily practice of primary health care and emergency departments, the results of this study can be generalized to other locations.

**Trial registration:**

(Trial registration at clinicaltrials.gov: NCT00809913 and trialregister.nl: NTR01583)

## Background

Fever in urinary tract infection (UTI) suggests the presence of tissue inflammation and is therefore considered to be a sign of acute pyelonephritis (AP) [1,2]. In 2000, the estimated direct and indirect costs of acute AP in the United States were $2.14 billion which is predominantly related to hospitalization [3]. In the last decades hospitalization rates of patients with AP has decreased from almost 100% to 10–30% [4-6]. The outpatient management of patients with AP has become popular as have oral antimicrobial treatment regiments and shortening of treatment duration [7-10]. However, such approaches have only been studied in the setting of uncomplicated AP, defined as AP in a young otherwise healthy non-pregnant woman without co-morbidity. In contrast to this, the optimal treatment of patients with complicated AP remains unclear and, not surprisingly, treatment guidelines therefore almost exclusively discuss uncomplicated AP [11,12]. Current strategies recommend antimicrobial treatment for at least 14 days [13-16].

Facing the aging of the general population it is challenging to better define the optimal treatment for AP in an unselected population including the elderly, men and patients with co-morbidity. Moreover, fluoroquinolones, being the preferred oral empirical treatment for AP, are associated with considerable side effects such as dysglycemia and *Clostridium difficile *infections, especially in the elderly and subjects with co-morbidity [17,18]. Therefore it is questionable whether the benefit of antimicrobial treatment of AP at the end of a 14-day antimicrobial treatment still outweighs its potential side effects.

We will conduct a multicenter, randomized, double-blind, non-inferiority trial to determine whether the efficacy and safety of a 7-day antimicrobial regimen is similar to a 14-day antimicrobial regimen in unselected individuals presenting with AP, defined as febrile UTI, at primary care or emergency department.

## Methods/Design

A randomized placebo-controlled double-blind multicenter trial is conducted with the aim to determine non-inferiority of the primary outcome measure between short treatment and standard treatment of febrile UTI. Consecutive patients will be randomized in a 1:1 ratio stratified per center and sex, to receive either a 7-day or 14-day regimen of antimicrobial treatment. Those enrolled in the 7-day regimen will be provided with placebo tablets to match antimicrobial tablets to complete a 14-day course.

### Patients

#### Inclusion criteria

A subject is eligible for inclusion if all of the following criteria apply: 1) Competent patient aged 18 years or above, 2) One or more solicited symptoms suggestive of urinary tract infection (UTI) (i.e. dysuria, frequency, urgency, perineal pain, suprapubic pain, costovertebral tenderness or flank pain), 3) Fever defined as a measured temperature ≥ 38.2°C (ear, rectal) or ≥ 38.0°C (axillary) and/or a history of feeling feverish with shivering or rigors including the past 24 hours, 4) Positive urine nitrate test and/or leukocyturia as depicted by leukocyte esterase test or the presence of more than 5 leukocyte per high- power field in a centrifuged sediment.

#### Exclusion criteria

A subject is not eligible for inclusion in this trial if any the following criteria apply: 1) Known allergy to fluoroquinolones, 2) Pregnancy or lactation, 3) Polycystic kidney disease, 4) Permanent renal replacement therapy, 5) History of kidney transplantation, 6) Residence outside country of enrollment, 7) Inability to speak or read Dutch and 8) Absence of written informed consent.

In addition to these exclusion criteria patients with the following conditions, indicating longer or other antimicrobial treatment, will not be randomized: 1) Isolation of ciprofloxacin-resistant causal uropathogen, 2) Presence of renal abscess, 3) Presence of underlying chronic bacterial prostatitis and 4) Presence of metastatic infectious foci.

A subject can be included in this study only once.

#### Setting

Patients eligible for this trial will be recruited at primary health care centers or at emergency department (ED) of hospitals in the Leiden region. The primary care region and participating hospitals serve one single area (North-West of South Holland) of the Netherlands (Figure 1). Patients considered ill enough by their primary care physician to require hospitalization will be enrolled at the emergency department of affiliating regional hospitals to which they refer.

**Figure 1 F1:**
[figure not shown]
**Geographic distribution of participating sites**.

### Treatment

Subjects will be randomized to receive either short antimicrobial treatment for 7 days followed by placebo for 7 days, or standard antimicrobial treatment for 14 days. The decision whether to treat as outpatient or inpatient will be made by the attending physician based on clinical judgment. Outpatients will be treated non-blinded with oral ciprofloxacin (500 mg b.i.d.) for 7 days followed by the blinded study medication (oral ciprofloxacin 500 mg or placebo b.i.d.) for 7 days. Inpatients will be empirically treated according to local guidelines on antimicrobial treatment (β-lactam ± aminoglycoside intravenously). After empirical intravenous treatment, patients will be switched as soon as possible to oral ciprofloxacin. Patients will then receive non-blinded oral ciprofloxacin (500 mg b.i.d.) up to the 7^th ^day followed by the blinded study medication (oral ciprofloxacin 500 mg or placebo b.i.d.) for additional 7 days. Inpatients that are empirically treated with oral antimicrobials will be treated as the outpatients. The placebo is indistinguishable from the ciprofloxacin containing formula, by sight and taste. Blinded treatment (ciprofloxacin 500 mg or placebo) is manufactured according to Good Manufacturing Principles principles by ACE Pharmaceuticals BV, Zeewolde, The Netherlands. Both the subject and investigator are blinded.

Patients with an indication of longer or other antimicrobial treatment as assessed by the additional exclusion criteria will be treated according to best clinical practice as judged by the attending physician. Though not randomized, these patients will remain in the study to assess the outcome.

### Data collection and management

Demographic, clinical and microbiological data will be collected by qualified research nurses or the clinical investigator ([name]) who will visit all patients at home directly after they have been notified by the primary care physicians. Data from patients included at the ED will be collected from the medical record completed with an interview by telephone or at the bedside using a standardized questionnaire. Blood and urine cultures will be taken before commencement of antimicrobial therapy and are analyzed by standard microbiological methods at local certified laboratories. All patients will be contacted by person at day of enrolment, 3–4 days and 28–32 days thereafter and are contacted by phone at 13–15 days and 84–92 days after enrolment to assess outcome. Urine cultures will be performed 28–32 days after enrolment to assess microbiological outcome. In case of (re)admission during the study period, related data will be taken from the medical record. A detailed flowchart of data registration is outlined in Table 1.

**Table 1 T1:** Flowchart of assessments in patients with acute pyelonephritis at time points during follow-up.

Evaluation	Days after Enrolment				
	
	0	3–4	13–15	24–32	84–92
**Notification to study center**	X				
**Entry criteria**	X				
**Written Informed Consent**	X*	X*			
**Demography**	X				
**Clinical data**	X	X	X	X	X
**(Serious) Adverse events**	X	X	X	X	X
**Mortality**		X	X	X	X
**Blood culture**	X				
**Urine culture**	X			X	
**Randomization and allocation to study treatment**		X			
**End of treatment assessment**			X		
**Contact – in person**	X	X		X	
**Contact – by phone**			X		X

Ad *: After notification at emergency department written informed will be obtained as soon as possible with a maximum till the 4^th ^day.

Data of clinical and microbiological data are collected in standardized questionnaires, case record files (CRFs), subjects' diaries and laboratory records. The data will be entered into a SPSS database using SPSS Data Entry Builder 4.0. To ensure validity of entrance the data will be inputted twice. All data sets will be initiated with an audit trail. The subjects' diaries are considered supportive for the investigators when filling in the CRFs, i.e. all relevant information will be translated and transferred to the CRFs by the research nurses or the clinical investigator. The data sets will be checked for consistency and plausibility. All ambiguous or implausible data items will be resolved by data queries to the investigators in the field.

### Randomization

A computer-generated randomization list of permuted blocks of 4 made by an appointed pharmacist will be used for treatment allocation. This list contains the numbers 1 to 500 and consists of 125 blocks of 4. The list of randomization numbers and corresponding treatment (placebo or ciprofloxacin) will be saved in an independent database with restricted access by the pharmacist. Stratification will be done per center site (7 hospitals; all primary health care centers are considered as one center) and sex. Each collaborating center will be allocated eight consecutive treatment packages consisting of 2 (one for males and one for females) consecutive blocks of 4, each time when needed. Randomization, and thus allocation to study treatment, will be done once the results of the urine culture become available at the 3^rd ^or 4^th ^day after inclusion.

### Endpoints

#### Primary endpoint

The primary outcome measure is clinical cure rate, defined as being alive with resolution of UTI symptoms and fever, among evaluable patients through the 10- to 18-day post-treatment visit.

#### Secondary endpoints

The secondary outcome measures are bacteriologic cure through the 10- to 18-day post-treatment visit, clinical cure rate through the 70- to 84-day post-treatment, all-cause mortality and adverse event rate determined 10- to 18 days and 70- to 84 days post-treatment, rate of UTI relapse and rate of adverse events during 90 days of follow-up. In addition, the outcome measures will be stratified according to final diagnosis as classified by the Infectious Diseases Society of America and the European Society of Clinical Microbiology and Infectious Diseases [19,20]. This includes analysis of specific subgroups, i.e., men, patients with acute complicated pyelonephritis, patients with any co-morbidity and patients with bacteremic UTI.

#### Definitions

The following definitions will be used. *Clinical cure *is defined as being alive with the absence of fever (temperature < 38.0°C) and the resolution of UTI symptoms (either absence of symptoms or at least 2 points improvement on a 0 through 5 points severity score) through the post-treatment visit whereas no additional antimicrobial therapy for a relapse of UTI is described. *Clinical treatment failure *is the opposite of clinical cure and defined as deterioration, persistent fever and/or symptoms of UTI (less than 2 points improvement on a 0 through 5 points severity score) or relapse of UTI with the same uropathogen for which additional antimicrobial treatment is prescribed. *Clinical recurrence *is defined as any clinical UTI after clinical recovery and the end of treatment period including uncomplicated UTI, complicated UTI and acute pyelonephritis as defined previously [19]. Based on microbiological typing of isolated uropathogen distinction will be made between clinical relapse, being the same uropathogen or clinical reinfection with a different uropathogen. *Pre-treatment significant growth of uropathogens *is defined as ≥ 10^4 ^colony forming units/mL in women (midstream urine) or ≥ 10^3 ^colony-forming units/mL in men (midstream urine) or ≥ 10^3 ^colony-forming units/mL (catheter urine) or ≥ 10^2 ^colony-forming units/mL of midstream urine collected during antibiotic treatment of UTI at study entry [19]. *Bacteriologic cure *or eradication is defined as the elimination of the study entry uropathogen or as pathogen growth of less than 10^4 ^colony forming units/mL in women or less than 10^3 ^colony-forming units/mL in men, of a midstream urine sample collected combined with the disappearance of leucocyturia [19]. *Bacteriologic failure *through the 10- to 18-day post-treatment visit is defined as the absence of bacteriologic cure and classified as persistence of the original pathogen or superinfection with a new pathogen on the basis of species determination and antibiogram or an alternative method, such as Amplified Fragment Length Polymorphism or sequence-based PCR using repetitive extragenic palindromic primers. *Ciprofloxacin resistance *of uropathogens is defined by a MIC > 4 mg/L and includes all *Enterococcus spp. Acute complicated pyelonephritis *is defined as febrile urinary tract infection in a person with one or more of the following baseline characteristics: male sex, postmenopausal (female aged ≥ 50 years), underlying urinary tract disorder (e.g. nephrolithiasis, urologic malignancy, vesicoureteral reflux, urethral stricture), diabetes mellitus, immunocompromised, renal insufficiency or progressive UTI despite antimicrobial UTI treatment. *Co-morbidity *is defined as the presence of any urinary tract disorder, heart failure, cerebrovascular disease, renal insufficiency, diabetes mellitus, malignancy or chronic obstructive pulmonary disease for which the patient is prescribed medication and/or consults a hospital-based medical specialist.

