### Safety

Adverse events will be monitored by passive self-reporting and active surveillance at each follow-up visit or telephone call; the rates of adverse events within the two treatment arms will be compared. Safety data will be subject to clinical review and summarized by appropriate descriptive statistics. In case of treatment failure the attending physician will prescribe additional antimicrobial treatment, as appropriate. Such 'rescue medication' will be offered by the study team.

An independent Data and Safety Monitoring Board (DSMB) will monitor safety on an ongoing basis throughout the trial. Safety reports summarizing Serious Adverse Events (SAE) will be submitted to the Chair of the DSMB after each SAE. In addition, the DSMB will review the results of the interim analyses scheduled to occur after approximately 25, 50 and 75 percent of the patients have completed until the 10- to 18-days post-treatment visit. The objective of the interim analyses is to consider stopping for safety reasons only. The breaking of the blind and the analysis of the data will be performed by a pharmacist and the members of DSMB. The following stopping rules are predefined during each interim analysis: 1). Regarding the primary outcome measure, Short treatment is definite inferior to Standard treatment with statistical significance of ≥ 95% certainty and 2). The clinical cure rate in the Standard arm is <75%. Besides these stopping rules, the judgment of the DSMB will be based upon a general review of adverse events including 30-day mortality. The initial communication to the study team will consist only of the outcome of the decision: either 1) there is sufficient evidence to consider stopping the trial or 2) there is insufficient evidence to consider stopping the trial.

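### Bacteriologic cure has no condition on additional antibiotics, so a patient retreated for UTI before the single follow-up culture can be scored as a cure of the allocated arm

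*Protocol article*

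**What the plan says.** All references are to the protocol article.

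- **Bacteriologic cure (Definitions).** It "or eradication is defined as the elimination of the study entry uropathogen". The alternative route is growth under a sex-specific threshold "of a midstream urine sample collected combined with the disappearance of leucocyturia".
- **Bacteriologic failure (Definitions).** Through the 10- to 18-day post-treatment visit it "is defined as the absence of bacteriologic cure and classified as persistence of the original pathogen or superinfection with a new pathogen". It is simply the complement of cure, and retreatment is not a criterion.
- **Clinical cure and failure (Definitions).** Cure carries the condition "whereas no additional antimicrobial therapy for a relapse of UTI is described" (the last word presumably means prescribed). Failure includes "relapse of UTI with the same uropathogen for which additional antimicrobial treatment is prescribed".
- **Endpoint status (Secondary endpoints).** "The secondary outcome measures are bacteriologic cure through the 10- to 18-day post-treatment visit". It is the first secondary outcome listed.
- **Culture schedule (Data collection and management).** "Urine cultures will be performed 28–32 days after enrolment to assess microbiological outcome". Table 1 labels the same visit day 24–32. The only other scheduled urine culture is at day 0; the day 13–15 contact is by phone and has none.
- **Rescue (Safety).** "In case of treatment failure the attending physician will prescribe additional antimicrobial treatment, as appropriate".

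**The concern.** Retreatment is part of the outcome for the clinical endpoint but is ignored in the bacteriologic one. Once a patient has been retreated, the later culture reflects the allocated treatment plus the rescue course. If that culture is clear, the definition as written credits the eradication to the allocated arm, and the same patient can be a clinical failure and a bacteriologic cure.

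The distortion acts on failures. If one arm produces more of them, more are available to be retreated and turned into cures, and the arms are drawn together. In a trial that aims to show that short treatment is not worse, that is the unhelpful direction. Readers are likely to look to this endpoint for microbiological support of the clinical result.

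**Working it through.** **1. Does the path exist on the text?** Set the provisions side by side for a patient who fails clinically after the end of active treatment:

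- Safety: additional antimicrobials are prescribed.
- Clinical definitions: relapse with the same uropathogen and retreatment makes the patient a clinical failure.
- Schedule: the next scheduled urine culture is at day 28–32 (text) or 24–32 (Table 1).
- Bacteriologic definition: if the entry pathogen is gone at that culture, the patient meets the first route to cure.

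No assumption is needed to show that this can happen. How often it happens is not in the document.

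**2. Time available for relapse and rescue.** Active drug ends at day 7 (Short) or day 14 (Standard). Before a culture at day 24–32, the time off active drug is 24 − 7 = 17 to 32 − 7 = 25 days in the Short arm and 24 − 14 = 10 to 32 − 14 = 18 days in the Standard arm. The Short arm has seven more days in which a relapse could occur and be treated.

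**3. Size.** The plan states no expected rate, margin or power for bacteriologic cure, so there is no planned figure to reproduce. The following is an illustration.

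Inputs:
- f_S, f_L: clinical failure in Short and Standard. From Sample size: 10.5% and 10% (cure 89.5% and 90%). Assumed unfavourable case: 20% and 10%.
- c = 60%: share of failures still carrying the entry pathogen when they fail (assumed).
- r = 50–80%: share of those retreated before the culture (assumed).
- s = 80–90%: share of the retreated whose urine is clear at the culture (assumed).
- r and s are taken as equal in both arms.

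Formulas: true gap = c × (f_S − f_L); observed gap = true gap × (1 − r × s).

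| r | s | 1 − r × s | 20% v 10%: true gap 0.6 × 10 = 6 points | 10.5% v 10%: true gap 0.6 × 0.5 = 0.3 points |
|---|---|---|---|---|
| 50% | 80% | 0.60 | 3.6 | 0.18 |
| 50% | 90% | 0.55 | 3.3 | 0.17 |
| 80% | 80% | 0.36 | 2.2 | 0.11 |
| 80% | 90% | 0.28 | 1.7 | 0.08 |

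The share of the gap lost is r × s, that is 40–72%, whatever the failure rates. The absolute loss is 2.4–4.3 points in the unfavourable case and 0.12–0.22 points at the planned rates.

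**4. Level in each arm.** At the planned rates the reported eradication rate rises by c × f × r × s. In Standard this is 6 × 0.40 = 2.4 to 6 × 0.72 = 4.3 points; in Short, 6.3 × 0.40 = 2.5 to 6.3 × 0.72 = 4.5 points. So at those rates each arm's reported rate moves by a few points while the difference hardly changes.

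**The case against.** **The word *through* may be cumulative.** Bacteriologic failure is assessed through the visit and includes persistence of the original pathogen. The Definitions also separate relapse from reinfection by typing isolates, which presupposes a culture at relapse. On that reading a relapse proven by culture is a bacteriologic failure whatever the later urine shows. This stands in part. But the article never says that an earlier positive culture overrides the visit culture, none is scheduled at failure, and the abstract words the endpoint as a rate at 10 to 18 days post-treatment. A patient retreated without a culture would still count as cured. The point is therefore limited to cases where no unscheduled positive culture is taken or counted.

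**Leucocyturia must also clear.** If that condition governs both routes, cure is harder to meet. A successful rescue course could satisfy it too, so it does not replace a retreatment condition.

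**This belongs in the analysis plan.** Handling of rescue for a secondary endpoint is often left there. Here, however, the article gives the definition in detail, with thresholds and typing methods, beside clinical definitions that do carry the condition. The stated definition itself gives the diluted result.

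**Using the culture as observed is a legitimate choice.** True, and scoring every retreated patient as a failure will include some whose urine was sterile when they were retreated. That is a reason to declare the strategy and show both analyses.

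**Stronger readings that the article does not support.**
- A reader might infer that this could falsely support the non-inferiority claim. That claim rests on clinical cure alone, which is lost through additional therapy for relapse. Bacteriologic cure has no margin, and UTI relapse is reported separately. In the 10% v 20% illustration the true clinical difference lies exactly on the 10-point margin, where the one-sided 0.05 test would declare non-inferiority only about 5% of the time.
- A reader might infer that rescue starts at once and that most failures are on, or just past, rescue at the culture. The Safety section gives neither timing nor duration. For a failure on day 12 the culture is 16–20 days later by the text (12–20 by Table 1).

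**Conclusion.** The point holds for a secondary endpoint. As written, bacteriologic cure ignores retreatment, and a patient retreated for UTI before the single follow-up culture can be counted as a cure of the allocated arm when no unscheduled positive culture is taken or counted. Any true difference between arms in this endpoint is then diluted toward equality. The primary endpoint is unaffected.

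The existence of the problem follows from the text; its size does not. Under the assumed inputs 40–72% of a true gap is lost. That is under a quarter of a point at the planned 90% v 89.5%, and 2.4–4.3 points if Short failure were 20% against 10%. These figures assume equal retreatment and clearance in both arms. With seven more days off active drug in the Short arm the shares could differ, and the simple factor would then no longer apply. The change is worth making because it is cheap and because the dilution is largest, in points, when the arms really differ.

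**What to change.** In Definitions, state for the main analysis of bacteriologic cure that:

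1. a patient given non-study antimicrobials for UTI between the start of blinded study drug and the 10- to 18-day post-treatment culture counts as a bacteriologic failure, whatever that culture shows, and is tabulated as a separate class (retreated before culture);
2. an unscheduled culture that grows the entry pathogen before the visit also counts as bacteriologic failure.

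Add a sensitivity analysis that uses the follow-up culture as observed.

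The cost is two sentences and one extra analysis. Retreatment data are already needed for the clinical endpoint. Sample size, visits and clinical management do not change. The downside is a slightly lower reported eradication rate, and some patients retreated with sterile urine will be counted as failures; the separate class and the sensitivity analysis make this visible.
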